| 0.15                 | 3.44 | 0.75                   | 2.58    | 2.97  | 351   | 0.42     | 843 | 0.15       | 970             |
| 0.2                         | 3.44        | 0.75                          | 2.58           | 3.10         | 202          | 0.42            | 485        | 0.15              | 558                    |

\*Adjusted for estimated bed net use and loss to follow-up

**5.2 Procedures***Recruitment, Randomization Process and Blinding*

Subjects will be recruited from villages in the Kintampo Health Research Centre (KHRC) study area once permission has been obtained from the village assemblies and elders, as well as the parent or guardian of the eligible child. Field researchers, employed by the KHRC, will visit individual households/compounds and interview parents or caregivers regarding the inclusion criteria. Once consent has been obtained and documented via signature or thumbprint, eligible children (one per household/compound) will be enrolled and randomized, using a computer-generated model, to either the iron (Fe) or placebo (P) group.

Sachets containing the powdered minerals with and without iron will look and taste identical with the exception that each package will be marked with an 'A' or 'B' denoting packages with or without iron. The study team and caretakers of children will be blinded to the 'A' or 'B' designation. Only the manufacturer of the powdered fortificant (in Ghana) and a research pharmacist each in Toronto and Kintampo will hold the key to the randomization and 'sachet' code lists. The key will be revealed to the 'Data and Safety Monitoring Committee (DSMC)' at the end of the first phase if a significant difference in outcomes is observed, and to the researchers after the database is closed and statistical analyses completed.

*Supply and content of the powdered mineral and vitamin fortificant.*

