##### Primary analysis

The primary outcome, incidence of malaria, will be compared between the two groups using Poisson regression. A 95% confidence interval for the ratio between the incidence in the iron group and the incidence in the placebo group will be calculated. The upper boundary of this confidence interval will be compared to the 10% tolerance limit. If it is lower, then non-inferiority can be concluded.

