##### Secondary analysis

Univariate Poisson regression with the same outcome will be used to evaluate associations with other variables: iron status at baseline, breast-feeding, age, gender and use of bed-net. These will then be introduced and re-evaluated in a multiple Poisson regression model, which will allow for adjusted group comparisons. Most importantly, by including the baseline iron status variable and the interaction with the main group variable, we can focus on the iron sufficient children that are receiving iron supplements and compare them against the others. The Poisson models will be validated by checking the model fit and for over-dispersion. Adjustments or transformations will be used if necessary.

The number of hospital admissions will be analyzed in a similar fashion, using Poisson regression. The parasite count outcome will be compared between the two groups, using a t-test. Univariate associations with other factors will be verified here as well, using t-tests, correlation coefficients and univariate regression.

Ultimately a multiple regression model will be developed, again for the purpose of adjusted comparisons between groups.

The normality of the data will be verified and, in the case of any departures, a log-transformation will be used and the data reanalyzed. If the log-transformation fails to achieve normality, a nonparametric alternative will be used instead. All statistical analyses will be carried out using SAS 9.1. The Analysis will be carried out on an intention-to-treat basis including all randomized children.

Upon the completion of the first intervention phase, an interim analysis will be performed by a Data and Safety Monitoring Committee (DSMC) as described above (primary analysis). The study will be stopped if the incidence of malaria is higher in one group.

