## **5.8 Potential Difficulties and Limitations**

a) Blinding: Although research staff will be blinded to the intervention, the stools of children receiving the iron containing fortificant will likely be darker (blackier) than those receiving the placebo. The applicants are unable to control for this likelihood.

b) If after the first phase (the dry season) there is more clinical malaria or more severe malaria or health complications in the group receiving the iron-containing fortificant, the DSMC may recommend terminating the study before the second phase begins.

c) It will not be possible to compare the results of the proposed current study to many of the results from the Pemba study. In Pemba, the primary outcome was mortality, which necessitated a sample size of more than 30,000 subjects. Also, in the current protocol, folic acid will not be included in the powdered mineral and vitamin supplement. Based on the estimated dietary folic acid intake of older infants and children in West Africa, folic acid deficiency should not be a problem (fruit is plentiful and inexpensive). Lastly, in the current protocol all children will receive and be encouraged to use bed-nets. This was not the case in the Pemba study.

d) Although studies in adults have suggested that elevations in TfR (82) or in ZnPP (75) can be definitive indicators of iron deficiency, there is large overlap in the distributions of these indicators in children with iron deficiency anemia as well as those with normal iron status. This overlap may be explained by a greater variability in the erythroid mass in children than in adults (83) together with the many variables affecting children in developing countries that influence TfR and ZnPP independent of iron status. Because of this overlap, the sensitivity and specificity of TfR and ZnPP in identifying iron deficiency and IDA may not be as high as we would prefer regardless of the diagnostic cutoffs chosen. Despite this limitation, all three biomarkers of iron status, ferritin, TfR and ZnPP, will be statistically evaluated individually and in groupings since this measure is very important in the context of the current study.

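### The DSMC gets the code key after phase I only if a difference is significant, so it cannot tell whether a non-significant excess lies with iron, although section 5.8(b) lets it act on such an excess

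*Protocol*

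**What the plan says.** Four places in the protocol bear on this.

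- **Section 5.2 (Recruitment, Randomization Process and Blinding).** There are two fixed codes: "each package will be marked with an 'A' or 'B' denoting packages with or without iron". Only the manufacturer and one research pharmacist each in Toronto and Kintampo "will hold the key to the randomization and 'sachet' code lists". The DSMC receives the key "at the end of the first phase if a significant difference in outcomes is observed". The section does not say which outcomes count, at what level, or who judges significance.
- **Section 5.5, Primary analysis.** The estimand has a direction. A 95% confidence interval is formed for "the ratio between the incidence in the iron group and the incidence in the placebo group", and its upper limit is compared with a 10% tolerance limit.
- **Section 5.5, end of Secondary analysis.** After phase I the DSMC itself performs an interim analysis by the primary method. The stopping sentence has no direction: "The study will be stopped if the incidence of malaria is higher in one group".
- **Section 5.8(b).** If the iron group shows more clinical malaria, more severe malaria or more health complications after the dry season, "the DSMC may recommend terminating the study before the second phase begins". No significance condition is attached.

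**The concern.** Section 5.2 makes knowledge of the arms depend on significance. Section 5.8(b) and the 10% comparison both need to know which arm is iron, significant or not. If the plan is followed as written, a committee looking at a non-significant difference sees an excess in A or in B and cannot say whether iron is the worse arm.

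The timing makes this important. Section 5.1 justifies the two-phase design by the DSMC's assessment of phase I results. The decision that follows is whether to enrol a second cohort in the higher-transmission season. Section 2 says that the study is not powered for the secondary outcomes, which include death and cerebral malaria. A significance gate is therefore a high bar for the rarer events among the grounds in 5.8(b).

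**Working it through.** **Inputs.** From section 5.1 and Table 1: placebo rate 3.44 × 0.75 = 2.58 episodes per child-year; 351 person-years; 15% increase; 80% power; 5% type I error with two tests. From 5.5: a limit of 10%, that is, a ratio of 1.10.

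**Step 1: reproduce the plan's figure.** Person-years per group = (z₁₋α/₂ + z₀.₈)² (λ₀ + λ₁)/(λ₁ − λ₀)², with λ₀ = 2.58 and λ₁ = 1.15 × 2.58 = 2.967.
- Two-sided α = 0.025 (0.05 halved for two tests): 9.505 × 5.547/0.387² = 352.0, against 351 stated. The other rows give 3021, 774 and 203, against 3017, 772 and 202.
- Two-sided α = 0.05 gives 290.7 and does not match.
- 351/(5/12) = 842.4 (stated 843), and 843 × 1.15 = 969.5 (stated 970 per group).

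So 351 is per group, and the level behind Table 1 is 2.5%. Both levels are carried below because 5.2 states none.

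**Step 2: what can be done masked.** Swapping A and B inverts the ratio and leaves the p-value unchanged. Rates, Poisson test and interval need no key, and neither does the direction-free stopping sentence in 5.5.

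**Step 3: how often the key stays closed.** Take malaria incidence as the trigger. Expected placebo events: 351 × 2.58 = 906. For true ratio R, SE = √(1/906 + 1/(906R)), and P(significant) ≈ Φ(log R/SE − z).

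| True ratio | log R/SE | Closed, 5% level | Closed, 2.5% level |
|---|---|---|---|
| 1.10 | 0.0953/0.0459 = 2.076 | 1 − 0.546 = 45% | 1 − 0.434 = 57% |
| 1.15 | 0.1398/0.0454 = 3.076 | 1 − 0.868 = 13% | 1 − 0.798 = 20% |

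The smallest significant observed ratio is about 1.094 (5%) or 1.108 (2.5%).

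**Step 4: how often the 10% verdict depends on the letter.** With no true effect, SE = √(2/906) = 0.0470, so the half-width of the 95% interval is 1.96 × 0.0470 = 0.0921 on the log scale. The limit is log 1.10 = 0.0953.
- The A/B and B/A upper limits both fall below 1.10 only if the log ratio is within ±(0.0953 − 0.0921) = ±0.0032, or 0.068 SE. The probability is about 0.054.
- The result is non-significant at 5% with probability 0.950.
- In the remainder, 0.950 − 0.054 = 0.896, the result is non-significant, one labelling passes and the other fails: about 90%. A simulation of Poisson counts gives 0.897.
- For a true 5% excess the simulation gives about 78%.

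Example: A/B = 0.97 has interval 0.884 to 1.064, which passes. B/A = 1.031 has interval 0.940 to 1.131, which fails. The p-value is 0.52, so the key stays closed.

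**Step 5: rarer outcomes.** The protocol gives no event rates for them, so these are assumptions. At 0.02, 0.1 and 0.5 events per person-year on placebo, the smallest significant ratio at the 5% level is about 2.4, 1.5 and 1.2.

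**The case against.** Several stronger readings are tempting, and the protocol does not support them.

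- **The DSMC cannot run the interim analysis.** A reader might infer this, but step 2 shows otherwise.
- **The grounds in 5.8(b) cannot be used at all.** Once a difference is significant the key is released and 5.8(b) works. At a true 15% excess, the difference that section 5.1 calls clinically significant, that happens in about 87% (5% level) or 80% (2.5% level) of interims.
- **Severe malaria is too rare ever to reach significance.** Section 5.1 defines severity of clinical malaria by level of parasitemia and 5.5 compares parasite counts by t-test. That is a continuous measure on many episodes. The difficulty with rare events applies to outcomes such as death and cerebral malaria, for which no rates are given.
- **Failing the 10% limit would have stopped the trial.** No section makes it a stopping criterion. It only means that non-inferiority is not concluded.

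There are also fair points in the plan's favour. Section 5.8(b) sits among limitations and is discretionary. Keeping a committee masked until there is a signal is a recognised choice. The trigger refers to outcomes in the plural, and a difference in anemia could release the key more often than step 3 suggests. Against that, the timetable in 5.9 lists only primary-outcome data being compiled for the DSMC. Finally, section 8.5 promises a detailed monitoring plan.

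These points narrow the finding but do not remove it. The sentence in 5.2 fixes the access rule in the protocol itself, and it conflicts with 5.8(b) for every non-significant excess.

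**Conclusion.** The concern holds in this limited form. Sections 5.2, 5.5 and 5.8(b) cannot all be followed when no difference is significant: the committee may act on an iron-group excess that it has no means of identifying, and it must compare an iron/placebo limit that it usually cannot orient.

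The size is 45% or 57% of interims with the key closed at a true 10% excess, and 13% or 20% at a true 15% excess, for the 5% and 2.5% levels. With no true effect, about 90% of interims give a non-significant result whose 10% verdict turns on which letter is iron.

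These figures rest on the planned person-years and rate, Poisson variation without over-dispersion, a Wald test on the log ratio, and malaria incidence as the trigger. A broader trigger would lower the closed-key percentages. The conflict between the sections does not depend on any of these assumptions. The protocol should be amended before phase I ends.

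**What to change.** Amend the key-release sentence in 5.2 so that the independent DSMC, or its unblinded statistician, has the key for the end-of-phase-I review whether or not a difference is significant. Investigators, field staff and caretakers stay blinded as now.

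Reconcile 5.2, 5.5 and 5.8(b) with one another. The stopping sentence in 5.5 has no direction and is mandatory, while 5.8(b) is directional and discretionary. The sponsor should state which governs, on which outcomes and at what level. This review does not propose the rule. The monitoring plan promised in 8.5 should carry the same wording.

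The cost is one amended sentence on key access plus the reconciliation. Dosing, sample size and field conduct do not change. The downside is one more party holding the key, which is usual for an independent committee.

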#### *Primary and Secondary Outcomes*

The primary outcome will be **clinical malaria**, defined (according to WHO criteria) as parasitemia (malaria parasites detected on a blood smear) of any density plus history of fever (within 48 hours) or axillary temperature  $>37.5^{\circ}\text{C}$ . Criteria for clinical malaria will be taken from the UNICEF Case Management Series, entitled, "Promoting Rational Use of Drugs and Correct Case Management in Basic Health Services – Malaria Prevention and Treatment" published by UNICEF's Programme Division in cooperation with the World Health Organization in 2000. To distinguish unique malaria episodes, treatment will be supervised and follow-up blood smears will be collected from the child as described below in Section 5.2(c).

Secondary outcomes will include: (i) changes in anemia status; (ii) the severity of the clinical malaria (based on level of parasitemia); (iii) cerebral malaria; (iv) hospitalization (from any cause) (v) death; (vi) pneumonia; (vii) diarrhea and dehydration.

*Subjects/study population*

Infants and young children (6-24 months of age), living in the Brong Ahafo Region of northern Ghana, will be included in the study if, at baseline, they are ingesting weaning foods in addition to breastmilk; free from malaria or other major illness; afebrile; living in the study area for the duration of the intervention and follow-up period; and if parental consent is obtained. Inclusion of a child into the study will proceed after the possible risks and benefits are discussed with the parents (in the appropriate local language), and a signed consent is obtained. The exclusion criteria are as follows: severe anemia (hemoglobin <70g/L), weight-for-height <-3 z-score (severe wasting), kwashiorkor (defined as evidence of edema), congenital abnormality, treatment with iron supplements in the past 6 months, or any chronic illness. Children that are severely anemic (Hb<70 g/L) and/or have symptoms of clinical malaria will be excluded from entry to the study and referred to the local health provider for treatment according to Ghana Ministry of Health guidelines.

*Sample Size*

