a) *Baseline:* After consent is provided, subjects will be screened for anemia (based on hemoglobin) and parasitemia. Enough blood will be taken to determine ferritin (SF), C-reactive protein (CRP), serum transferrin receptor (TfR) and zinc protoporphyrin (ZnPP). Those who are severely anemic (Hb <70 g/L), or have clinical signs of infection (including malaria) will be referred to the study clinician who will offer the child the standard care, as defined by the Ghana Ministry of Health. All other children will be enrolled and randomized to either the iron (Fe) or placebo (P) group. The child's weight and length measurements will be recorded, as well as any relevant demographic (age, gender) and historical health information (birth weight, immunization status, and previous hospitalizations). Caregivers will also be asked to provide information regarding their usual feeding practices and health-seeking behaviours. All households will be provided with a treated bed net and a supply of powdered fortificant with oral instructions on how to use each.

*b) Monitoring visits:* Field researchers will visit each subject at their home every week in the first month of the study and at 4 week intervals for the next 4 months. At each visit, the field researcher will conduct a health assessment (including axillary temperature) and collect information on feeding history, supplement compliance, bed net use and morbidity. At the initial weekly visits, 7 new sachets will be provided, and then at the start of the second month, 30 new sachets will be provided to last for a month. Clear instructions for storage and administration of sachets will be provided to families. All used and unused sachets will be counted and recorded. It has been our experience in other similar studies in Ghana and elsewhere that by providing pre-emptive information on the impact of the fortificant to parents (like telling parents that stools will darken from the iron, and that children will become more active and have enhanced appetites), the adherence to the use of the sachets is generally in the range of 70 – 98%. We will provide this pre-emptive information in the current study.

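### The protocol's entry rules disagree on severe wasting and on an afebrile child with a positive baseline smear, and baseline parasitaemia is absent from the adjusted model

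*Protocol*

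**What the plan says.** Four places in the protocol bear on who may be randomised.

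- **Section 5.1, Subjects/study population.** At baseline the child must be "free from malaria or other major illness; afebrile". The exclusions add severe anaemia, "weight-for-height <-3 z-score (severe wasting), kwashiorkor (defined as evidence of edema), congenital abnormality, treatment with iron supplements in the past 6 months" and chronic illness. The malaria exclusion is then restated in terms of symptoms: "Children that are severely anemic (Hb<70 g/L) and/or have symptoms of clinical malaria will be excluded from entry to the study".
- **Section 5.2, Recruitment.** Field staff interview caregivers about the inclusion criteria, and randomisation is confined to eligible children.
- **Section 5.2, Clinical protocol, a) Baseline.** Blood is tested for haemoglobin and parasitaemia. Children with haemoglobin below 70 g/L or clinical evidence of infection go to the study clinician. Then: "All other children will be enrolled and randomized to either the iron (Fe) or placebo (P) group". The next sentence reads in part "The child's weight and length measurements will be recorded". The paragraph does not mention an oedema check.
- **Section 8.1a.** Children must meet the earlier criteria and show no clinical evidence of infection at enrolment.

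The primary outcome in section 5.1 is "parasitemia (malaria parasites detected on a blood smear) of any density plus history of fever", or a raised axillary temperature in place of the fever history. The adjusted model in section 5.5 lists baseline iron status, breast-feeding, age, gender and bed-net use.

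**The concern.** A field team following the baseline paragraph as written would not apply the whole section 5.1 list. Severe wasting and oedema are entry exclusions in a trial that gives iron to young children, yet the paragraph that leads to randomisation does not invoke them. A caregiver interview cannot supply a weight-for-height z-score.

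The baseline test for parasitaemia has no stated consequence, so the text leaves open whether silent carriers belong to the trial population. That matters for the endpoint. A child still carrying parasites can meet the case definition with a fever of another cause. The smears on days 3, 7, 14 and 28 in section 5.2(c) follow treatment, so they do not show whether a child's first counted event came from an infection present at entry. Section 5.5 concludes non-inferiority if the upper 95% limit of the rate ratio lies below a 10% tolerance, so dilution towards 1 favours declaring iron safe.

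**Working it through.** **Step 1. The entry rule for two kinds of child, neither with severe anaemia nor clinical signs of infection.**

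| Child at baseline | 5.1 | 5.2 Recruitment | 5.2 Baseline | 8.1a |
|---|---|---|---|---|
| Weight-for-height below -3 z, or oedema | Out | Out only if already judged ineligible; the interview cannot give a z-score | In, read literally | Out, by reference to the earlier criteria |
| Afebrile, smear-positive | Out if malaria-free means smear-negative; in if it means no clinical malaria | Not addressed | In | In |

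The first row is a mismatch between the exclusion list and the baseline procedure. The second is a firm contradiction only if malaria-free means smear-negative. Section 5.1 lists afebrile separately, which leans towards that reading, but nowhere defines the term.

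**Step 2. Evidence in the protocol that baseline smear matters.** Section 3.1 reports a pooled odds ratio for smear positivity of 1.43 (1.08-1.91), which becomes 1.24 (0.98-1.57) after adjustment for baseline smear. The section 5.5 covariate list omits baseline parasitaemia, although section 5.2 collects it.

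**Step 3. The plan's own figure.** Table 1 uses r0 = 3.44 x 0.75 = 2.58 and r1 = 2.58 x 1.15 = 2.967 episodes per child-year. Person-years per group = (z[1-alpha/2] + z[0.80])^2 x (r0 + r1)/(r1 - r0)^2. With two-sided alpha 0.025 (0.05 split over two tests) this is (2.2414 + 0.8416)^2 x 5.547/0.387^2 = 352, against 351 stated. Then 351 x 12/5 = 842.4, taken as 843, and 843 x 1.15 = 969.4, taken as 970 per group. The design figures reproduce, and this point does not change them.

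**Step 4. Illustration of dilution (assumed inputs).** Let a share f of counted placebo episodes be incidental and equally frequent in both arms. The observed ratio is f + (1 - f) x 1.15. Power uses 351 person-years per group at alpha 0.025. False non-inferiority is the chance that the upper 95% limit falls below 1.10 in one cohort when the true malaria ratio is exactly 1.10. Where two values stand, the first holds the total placebo rate at 2.58 and the second adds incidental events on top of 2.58.

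| f | Observed ratio if true 1.15 | Power | False non-inferiority |
|---|---|---|---|
| 0% | 1.150 | 80% | 2.5% |
| 5% | 1.143 | 75% / 78% | 3.1% / 3.2% |
| 10% | 1.135 | 71% / 76% | 3.9% / 4.0% |
| 20% | 1.120 | 59% / 70% | 5.9% / 6.5% |

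To relate f to entry status, assume 10-50% of children are smear-positive at entry and 20-40% of those have a countable incidental fever. That gives 0.02-0.20 events per child against 2.58 x 5/12 = 1.075 expected. The share is 0.02/1.095 = 1.8% to 0.20/1.275 = 15.7%, and a true 1.15 becomes (1.15 x 1.075 + 0.02)/1.095 = 1.147 to (1.15 x 1.075 + 0.20)/1.275 = 1.126. Neither the prevalence nor the fever risk is in the documents.

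**The case against.** The strongest reply is that the section 5.1 exclusions remain in force throughout. Section 5.2 randomises only eligible children and section 8.1a refers back to the criteria. The baseline paragraph then describes what happens after the blood screen and cancels nothing. Its order of sentences is not an order of procedures: the sentence on weight and length also records age, which is itself an entry criterion. This stands. A reader might infer that only two checks are ever applied, or that wasted children will in fact be enrolled, and the documents support neither. What survives is that no passage places anthropometry or an oedema check before randomisation.

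On malaria, three of the wordings speak of symptoms or clinical signs, so the intended rule may be that only clinical malaria bars entry. That is a fair reading, but the text should say so. A reader might also expect sites to apply the rule differently; field work is run by one centre in one catchment area, so that does not follow.

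On the endpoint, two replies have force. Section 3.1 proposes that free iron helps parasites already present to multiply, so progression from silent carriage to fever may be the very harm under study and need not be equal between arms. And at the 269 infective bites per person per year given in section 4, children negative at entry can also become silent carriers, so most of the misclassification lies in the any-density definition. Treatment of smear-positive entrants is also unstated; section 5.3 says rapid tests help decide on treatment, so persistence of the baseline infection is an assumption.

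Finally, a subgroup analysis can be left to an SAP. The covariate list, however, is fixed in the protocol.

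**Conclusion.** The inconsistency is in the text and should be corrected before enrolment. For severe wasting and oedema, the baseline procedure read literally does not apply a stated exclusion. For the afebrile smear-positive child, eligibility is ambiguous, and contradictory if malaria-free means smear-negative.

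The effect on the primary comparison is possible but unquantified. Its direction is towards a ratio of 1 only if incidental events are equally frequent in both arms, and the figures in the working rest on assumed shares.

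A reader might go further and conclude that early febrile parasitaemia in smear-positive entrants should not be counted for 28 days. The documents do not support this. Day 28 in section 5.2(c) is a smear after treatment, not an episode window from enrolment, and dropping those events could remove the harm that section 3.1 hypothesises.

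**What to change.** Reconcile sections 5.1, 5.2 and 8.1a into one eligibility list applied in full before randomisation, and place the weight, length and oedema checks ahead of it. State what a positive baseline smear means for entry; which rule to adopt is for the investigators.

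If smear-positive children may enter:

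- pre-specify the primary rate ratio by baseline smear status, including the estimate in smear-negative children;
- add baseline parasitaemia to the adjusted Poisson model in section 5.5;
- keep all events in the main analysis.

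The cost is protocol wording, an explicit order for the baseline visit and slightly more analysis. The baseline parasitaemia test and the anthropometry are already planned, and the oedema check is already implied by the exclusion. Estimates within smear groups will be less precise than the overall ratio, so they serve as supporting results.

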*c) Follow up:* At the end of 5 months, subjects will again be screened for anemia, ferritin, CRP, serum transferrin receptor, zinc protoporphyrin and a blood smear for their malaria status. The subjects will be weighed and measured, and caregivers will again be asked about feeding history, supplement use, and bed net use. Any remaining sachets will be collected and counted. All families that have completed the intervention will be provided with a study closure package (including some rice and soap) as has been the standard goodwill practice of KHRC to participants from the communities. For those children who are anemic, based on their end-line hemoglobin assessment, an additional 60 sachets of iron-containing powdered fortificant will be provided. Providing iron to anemic children is not a safety issue in this case because they will be eligible for treatment according to the WHO statement on the use of iron in malaria endemic areas (3).

*d) Discontinuation of supplementation.* Supplementation will be stopped if any of the following is reported: admission to the hospital ward for >5 days; evidence of chronic diarrhea (defined as loose stools lasting >4 weeks); prolonged fever of unknown origin; emergence of any exclusion criteria after randomization. Prompt, daily disclosure by field workers of any concerns will be encouraged. If necessary, children will be referred to local physicians for treatment according to local standards. Reasons for stopping supplementation voluntarily will be recorded.

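### The caregiver message ties dark stools to iron and each arm carries one fixed letter, so the protocol makes a conceded blinding weakness worse than it has to be

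*Protocol*

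**What the plan says.** **Caregiver message.** Section 5.2, Monitoring visits, describes advance information for parents, "like telling parents that stools will darken from the iron, and that children will become more active and have enhanced appetites", and then commits to it: "We will provide this pre-emptive information in the current study". The stated reason is adherence, put at 70–98% in similar studies. No restriction by arm is given. Since caregivers are to be blinded, the message could not sensibly differ by arm.

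**Coding.** Under Recruitment, Randomization Process and Blinding in section 5.2, "each package will be marked with an 'A' or 'B' denoting packages with or without iron". The same paragraph says "The study team and caretakers of children will be blinded to the 'A' or 'B' designation". Two codes therefore serve the whole trial.

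**Conceded limitation.** Section 5.8(a) expects darker stools on iron and adds "The applicants are unable to control for this likelihood". It mentions neither the message nor the coding.

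**Outcome.** Section 5.1 defines clinical malaria as parasitemia of any density "plus history of fever (within 48 hours) or axillary temperature" above a threshold. Under Tracking the subjects in section 5.2, a blood sample follows when fever is reported or recorded, and ill children are identified when they attend a facility. Home visits are weekly in month 1 and 4-weekly for the next four months. At each one the field researcher takes axillary temperature and collects morbidity and compliance data; sachets are supplied and counted on the same schedule.

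**The concern.** Caregivers are meant not to know their child's arm, yet they are told which visible sign comes from iron. A family that sees dark stools is pointed towards iron, and a family that was promised dark stools and sees none is pointed towards placebo. Because one letter covers a whole arm, a correct inference about some children carries over to all children with that letter. The people best placed to make it are field researchers, who see many children, handle the letters and collect outcome data.

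Knowledge of the arm can change how readily fever is reported, how soon a child is taken to a facility, and how well the powder is used. Section 8.1c lists possible higher malaria risk on iron for non-anemic children and on placebo for anemic children, and section 8.2a says parents are told of risks. Families could therefore react in either direction. The primary analysis judges a rate ratio against a 10% limit, so a modest difference between arms in how many episodes are captured matters. Intention-to-treat analysis and a larger sample do not remove that kind of bias.

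**Working it through.** **1. Inputs.** From section 5.1, Table 1: rate without iron 3.44 × 0.75 = 2.58 episodes per child-year; least meaningful difference 15%; 351 person-years per group; 843, then 970 children per group per cohort. From section 5.5: 95% CI for the rate ratio, with its upper bound compared with 1.10.

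**2. The plan's own figure.** With rates 2.58 and 2.58 × 1.15 = 2.967, 80% power and two-sided alpha 0.025 (0.05 shared over two tests):

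PY = (2.241 + 0.842)² × (2.58 + 2.967) / (0.387)² = 352.0, against 351 stated. Then 351/(5/12) = 842.4, i.e. 843, and 843 × 1.15 = 970. The table is reproduced; it serves here only to set the precision.

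**3. Precision of one cohort.** Placebo episodes E0 = 2.58 × 351 = 906. At a ratio of 1.00, SE(log ratio) = √(2/906) = 0.047, so the 95% CI is 0.91 to 1.10.

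**4. Effect of unequal capture.** Let R be the true ratio and c the share of episodes captured on iron relative to placebo. **The values of c are assumptions; the documents give none.** With plain Poisson variance:

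- Expected observed ratio = R × c, with SE = √(1/E0 + 1/(E0·R·c))
- P(non-inferiority) = Φ[(ln 1.10 − ln(R·c))/SE − 1.96]
- P(significant excess on iron) = Φ[ln(R·c)/SE − 1.96]

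| R | c | Expected ratio | P(non-inferiority) | P(excess detected) |
|---|---|---|---|---|
| 1.15 | 1.00 | 1.150 | 0.2% | 87% |
| 1.15 | 0.95 | 1.092 | 3.5% | 49% |
| 1.15 | 0.90 | 1.035 | 26% | 11% |
| 1.10 | 1.00 | 1.100 | 2.5% | 55% |
| 1.10 | 0.95 | 1.045 | 20% | 16% |
| 1.10 | 0.90 | 0.990 | 61% | 1.5% |
| 1.00 | 1.00 | 1.000 | 53% | 2.5% |
| 1.00 | 1.05 | 1.050 | 17% | 18% |

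Example, R = 1.15 and c = 0.95: the observed ratio is 1.0925 and SE = √(1/906 + 1/989) = 0.046. Then 0.0885/0.046 − 1.96 = −0.04, which gives 49%.

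**5. How readily a letter is identified.** The frequencies of dark stools are also assumptions. If a proportion s of iron children and b of placebo children show them, one dark stool points to the right letter with probability s/(s + b). The last column compares 10 children per letter and picks the letter with more dark stools, ties counting one half.

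| s | b | One stool | 10 per letter |
|---|---|---|---|
| 50% | 20% | 0.71 | 0.92 |
| 30% | 10% | 0.75 | 0.87 |
| 50% | 2% | 0.96 | 0.998 |

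**6. Dependence on caregivers.** After month 1, a 48-hour fever window at one home visit every 28 days covers about 2/28 = 7% of days. Most other detection starts with a caregiver's report or a facility visit.

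**The case against.** The protocol does not hide the cue: section 5.8(a) states it. The darkening comes from the iron, not from the message, and the message serves adherence. The outcome has an objective core, because a positive smear is always required and slides are read twice by independent microscopists, with a third for disagreements. A smear is the rule once fever is reported or recorded, and a temperature measured at a home visit counts without any caregiver report. Only one child per household or compound is enrolled, so a family has no second trial child at home to compare.

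Much of this stands, and it rules out several stronger readings that a reader might infer:

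- *That one dark stool unblinds the trial.* Section 5.8(a) says only that darker stools are likely, so a single stool is probabilistic evidence. Comparison across children by staff is the plausible route.
- *That an episode counts only if the caregiver reports it.* Measured temperature also qualifies.
- *That 5% under-capture makes a true 1.15 pass as non-inferior because it appears as 1.09.* Section 5.5 tests the upper confidence bound. At 1.0925 the CI is 0.998 to 1.196, so non-inferiority is not concluded.
- *That the end-line supply reveals the code.* Section 5.2 says "an additional 60 sachets of iron-containing powdered fortificant will be provided" to anemic children, but not that these come from trial stock or carry a letter.

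What the objection does not reach is that the wording and the two-letter scheme are choices, and section 5.8(a) addresses neither. Double reading protects the reading of a slide, not whether one is taken.

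**Conclusion.** The point holds as an avoidable weakness in blinding. Telling caregivers in both arms that iron darkens the stools, together with one fixed letter per arm, makes it likely that field staff could learn the meaning of the letters from a handful of children. Part of the primary outcome's ascertainment is open to that knowledge, especially between 4-weekly home visits.

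The documents show neither that bias will occur nor its size or direction. If 5% fewer iron-arm episodes were captured in one cohort, the chance of detecting a true 15% excess would fall from about 87% to 49%. At a true ratio of 1.10, false non-inferiority would rise from 2.5% to about 20%. If 5% more were captured, a true ratio of 1.00 would show a false excess 18% of the time instead of 2.5%. These figures rest on assumed capture ratios, the Table 1 rate, 351 person-years per group, plain Poisson variance and the 95% CI of section 5.5.

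**What to change.** - **Coding.** Replace the two letters with individually numbered packs, or several non-informative codes per arm, and use new codes in Phase II. This has to be settled before the sachets are made.
- **Message.** Give one neutral message in both arms, that stool colour may change with the powder, without tying it to iron. Parents are still warned, so most of the adherence rationale in section 5.2 is kept.
- **Optional check.** Record the caregiver's and the field researcher's guess of allocation at end-line, so that the success of blinding can be reported.
- **Section 5.8(a).** Limit the statement about lack of control to stool colour itself, and name the steps above.

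The cost is a longer code list for the manufacturer and the two pharmacists, slightly more complex stock handling, and possibly a small effect on adherence from the softer message.
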